#### Neurocognitive assessment app

Given the relationship between anxiety and inhibitory control and risk avoidance, youth will complete two neurocognitive tasks to measure these domains. One of the best-known paradigms to test inhibitory control is the Eriksen flanker task [95]. The flanker task requires learning novel associations between certain stimulus properties and responses to perform the task. Irrelevant stimuli must be inhibited while responding to the relevant target stimuli. The flanker task has been validated across varying development stages [96–98] and is frequently used in studies involving youth patients with anxiety disorders [99–101]. We created a youth-friendly version of this classical paradigm [102]. Youth will be presented with five fish and instructed to identify the swimming direction of the middle fish (relevant target stimuli) as quickly and accurately as possible while disregarding other fish (irrelevant stimuli) using a button in the app. The task estimates inhibitory control based on reaction times and accuracy.

The second task is the youth friendly Balloon Analogue Risk Task (BART) [103], a widely used neurocognitive paradigm to study risk-taking behaviour [104, 105]. The BART has been demonstrated to validly measure risk-taking in children, adolescents and adults; [105–108] it is also sensitive to development-related changes in risk-taking [109]. Presented with a balloon, youth can repeatedly pump up the balloon to increase their earnings or stop pumping and collect their accumulated earnings. The more pumps the participant makes increases the likelihood that the balloon will pop, resulting in a loss of all earnings. The average number of pumps across all trials will be recorded with increased pumps reflecting increased risk-taking proclivity [110] and lower numbers indicating increased risk avoidance.

As youth with anxiety disorders are likely to be affected by the presence of an unknown examiner [111], and to increase accessibility, we developed the GAYA app for administering the neurocognitive tasks. Co- designed with youth, the GAYA app allows youth participants to complete the tasks remotely in an environment of their choosing. The app can be installed on smartphones and tablets with iOS or Android operating systems. Participating youth will be provided with a download link for the app and their personal login credentials by the study team.

#### Saliva samples

Saliva sample collection will follow established protocols. Saliva-derived DNA has been shown to perform nearly as well as blood DNA [112, 113] and is routinely used in large-scale genetic studies in youth [60]. Youth will be invited to provide saliva samples at the nearest individual recruitment sites (Calgary, Halifax, Hamilton, or Vancouver) with an OG-600 Oragene saliva DNA sample kit or choose to have an OCR-100 ORAcollect DNA sample kit mailed to their home with a pre-paid return envelope. De-identified research IDs will link data and saliva samples. The linked IDs will be logged in REDCap to document and track the handling of biologic samples. Participants will be instructed on how to provide a sample by a trained research staff member via live video or a pre-recorded video and receive written instructions. Toronto participants will have already provided their saliva samples at the time of participating in Spit for Science using OG-600 Oragene saliva DNA sample kits.

### Optional intervention

#### Intervention procedures

Youth enrolled in GAYA who are ages 13–19, not currently in mental health treatment, and do not endorse psychosis screening questions will be offered the opportunity to participate in a self-managed Internet-based CBT (iCBT) program, Breathe (Being Real, Easing Anxiety: Tools Helping Electronically) [114], at all recruitment sites. These youth will be linked to the Strongest Families Institute (SFI, http://strongestfamilies.com/), where all referred youth will receive the Breathe program that is part of SFI’s validated eplatform IRIS (Intelligent Research and Intervention Software).

Through weekly self-managed check-ins, during which youth assess and rate their social-emotional functioning over the past week, a detailed monitoring of anxiety symptoms over the course of the Breathe program will be enabled. Youth will also be asked to rate their anxiety symptoms based on the SCARED pre-, post-treatment, and at a 3 months follow-up. Intervention response will be defined as the changes in SCARED scores from pre- to post-treatment for the 3 months follow-up.

#### Breathe intervention description

Breathe is a self-mediated 6-module standardized iCBT program that involves: (a) multimedia-based education about anxiety problems and approaches to overcoming anxiety (e.g., reviewing why exposure exercises are important); (b) self-assessment activities to determine level of intervention and safety needs; (c) activities that teach users about anxiety sensitivity and how to develop realistic thinking about anxiety-producing situations; (d) activities for practicing coping and relaxation skills; (e) development of a hierarchy of feared situations and steps for gradual and repeated exposure to feared situations (using imagery/in vivo activities); (f) contingency management (examining the function of anxiety from a reinforcement perspective) and modelling (viewing videos of others confronting feared situations); and (g) skills for maintenance and relapse prevention. Animations, embedded videos, timed prompts, and on-screen pop-ups are used in each module to provide an interactive and multimodal experience. In one of the largest effectiveness trials of iCBT in adolescents conducted to date, that used SFI’s IRIS eplatform, 563 adolescents aged 13–19 were randomly assigned to 6 weeks of Breathe (*n* = 280) or to visit a static (no elements of interactivity or personalization) website which provided resources for anxiety (*n* = 283) [115]. In the trial, adolescents who participated in Breathe had a greater improvement in symptoms 3 months after program use (*p* = 0.04) [115]. Although this Breathe study was complimented by one telephone coach support session to those who wanted the additional support, the current study will only be self-mediated.

### Collection of biomaterials, DNA extraction and genotyping process

DNA extraction from saliva is performed at each individual site following best practice and according to the manufacturers’ protocols. Subsequent genotyping will be performed in 3 batches. All individuals will be genotyped (using DNA from the saliva samples) with Illumina’s Global Screening Array v3.0 (GSA). The GSA is a cost-effective genotyping array that is routinely used for population-scale genetic studies around the globe. For genotyping calling Illumina’s GenomeStudio will be used. Spit for Science genotyping will be done locally using the same Illumina array and their genetic data is sent to the Halifax site once the participant has completed the questionnaires and/or app portion of the study.

### Quality control (QC) and imputation of GWAS data

The Ricopili pipeline will be used to perform QC of the genetic data within and across ancestral stratified subgroups (based on demographic information) [116]. Ricopili has been extensively used by international consortia for their large-scale GWAS and makes use of well-established analytic software during its processing steps (e.g., PLINK [116]). Analyses will look for any (hidden) *relatedness* or sample duplicates as part of our QC and flag individuals that are related (pi_hat > 0.2) for downstream analyses. Population substructure will be (re-) examined by principal components (PC) estimation and support vector machines will be run in joined PC analyses with a reference sample of known ancestral background (TopMed) to annotate the sample with population substructure information and compare this information with the demographic information collected during the online assessment. For *imputation*, a pre-phasing/imputation stepwise approach as implemented in Ricopili [117] will be used with and across population subgroups identified in our sample. This will include the evaluation of a potential increase in power through usage of imputation approaches that use local ancestry to enable inclusion of admixed individuals in the GWAS [118]. *ChrX* imputation will be conducted separately by sex for subjects passing an additional QC designed for these purposes [119]. For downstream analyses SNPs that have an INFO > 0.8 and a MAF > 0.01 will be considered.

### Data analysis strategy

Appropriate covariates (e.g., age, sex, gender, recruitment procedure/site) will be included for analyses in each trait. Where necessary and appropriate analyses will control for current/past treatment history through established protocols. For all GWAS, the impact of population substructure on the genome-wide test statistics using λGC [120] and Linkage Disequilibrium score regression (LDSC) analyses [121] will be evaluated. There are clear sex differences described in the epidemiology of anxiety. Anxiety disorders and symptoms occur more often in women, and the odds of developing an anxiety disorder is 1.7 times greater for women than men [122]. The analyses will therefore be stratified by sex and gender to explore shared and unique genetic contributions.

Data analysis will be aligned with each of the specific aims. For all results identified in aims 1–4, using MAGMA [123] and LDSC [124] tissue and single cell enrichment analyses will be conducted compiling publicly available single-cell RNA-sequencing data from five studies of the human and mouse brain [125–128]. Similarly, transcriptome-wide association studies will be conducted using FUSION [129] and expression quantitative trait locus data from the PsychENCODE Consortium (1,321 brain samples) [130]. In addition, analyses will include EpiXcan [131], an elastic net-based method, which weighs SNPs based on epigenetic annotation information [132].

#### Specific aim 1: identify genetic risk factors associated with clinical symptoms and vulnerability markers of youth anxiety

Following best practices in the field, additive model GWAS analyses will be conducted for common SNPs and each quantitative trait. To increase power, multivariate-based approaches will be employed that enable us to address the complex relationship of the anxiety phenotypes (SCARED subscales, BIS/BAS subscales, inhibitory control, and risk avoidance) amongst each other but also in relationship to the genetic data. As such the GW-SEM software package [133, 134] will be used. Genome-wide results from GAYA study samples will be meta-analysed with other available samples [25, 61] using inverse-variance weighting with METAL [135] and accounting for population structure. Sensitivity analyses using structural equation modelling (SEM), via genomic SEM, will help to address potential heterogeneity. Established approaches (LDSC [120] and GCTA [136]) will be used to study liability-scale heritability of clinical symptoms and vulnerability markers of youth anxiety. Partitioned heritability across minor allele frequency bins and functional annotations (e.g., cell-types) using the same software packages and publicly available data (e.g., from the PsychENCODE consortium [137]) will provide further insights into the genetic relationship of different clinical symptoms and vulnerability.

#### Specific Aim 2: identify genetic factors that are unique to anxiety in different age groups

Multi-trait conditional and joint analysis [138] to adjust GWAS summary statistics from the GWAS in youth for the genetic effects in adult anxiety to identify putative age group-specific SNP associations. It is noteworthy that previous analyses in closely related traits of similar sample size (e.g., ADHD) were able to identify new genome-wide significant hits specific to the traits under analysis [138]. Similarly, summary statistics from youth and adult anxiety GWASs will be analysed with ccGWAS [139], a tool designed to identify loci with different allele frequencies among different trait groups. Using ccGWAS genetic loci will be identified that are specific in their association to the individual age groups.

Using established protocols (SBayesR [140]/LDpred2 [141]/PRSice2 [142]) genomic risk profile scores (GRPS) will be generated in the GAYA study sample trained on discovery datasets from different age groups (i.e., pairwise between the youth and adult GWAS) to assess the variance explained through genetic liability for anxiety disorders in one age group for the other. Finally, where appropriate, CLiP [143] will be used to study heterogeneity in GRPS for the GAYA study sample.

#### Specific aim 3: identify genetic factors that are shared and unique between anxiety and its common comorbidities

Via LDSC [120] patterns of genetic correlation, common comorbidities (e.g., MDD, ADHD) with youth anxiety will be analyzed. Genomic SEM will be run including the youth anxiety GWAS along with the newest adult anxiety GWAS [21–23] to investigate the multivariate genetic architecture across youth anxiety and its comorbidities. In this multivariate GWAS, it will be possible to identify loci that confer risk to multiple disorders (i.e., that are shared across disorders).Two-sample Mendelian Randomization (MR) analyses will be conducted using the inverse-variance-weighted (IVW) MR method to investigate associations between the genetic liability for youth anxiety and adult-onset mental disorders, while further ensuring the robustness of our IVW estimates through MREgger and the MR robust adjusted profile score approach [144, 145].

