The most well-researched source of genetic variation known to influence the risk of psychiatric disorders are common single nucleotide polymorphisms (SNPs). Genome-wide association study (GWAS), which enables the search for risk variants across the genome, is ideally suited to study common genetic risk factors for polygenic conditions such as anxiety disorders. GWAS for specific anxiety disorders and traits were historically severely underpowered [13]. To overcome sample size limitations, researchers started analyzing disorder subtypes together. By meta-analyzing the results of 7 GWAS on 5 clinically ascertained anxiety disorder subtypes (*n* = 17,310), the ANGST Consortium study [21] identified 2 genome-wide significant loci. A GWAS in the UK biobank on composite anxiety phenotypes using self-reported symptoms and diagnoses (*n* = 83,566) identified 5 genome-wide significant loci [22]. In addition, the largest anxiety GWAS to date was performed in 175,163 European and 24,448 African military veterans using a 2-item dimensional measure of GAD [23]. The study identified 6 significant loci for anxiety in European Americans and one in African Americans. But GWAS studies of anxiety phenotypes in youth have thus far been unsuccessful in identifying any genome-wide significant loci due to reasons such as low power and heterogeneity [24–26].

Genetic correlations can guide our understanding of the nature and patterns underlying complex traits and disorders. Large GWAS of anxiety disorders show strong positive genetic correlations with major depressive disorder (MDD) (rG = 0.78) [22, 23]. Accounting for comorbid MDD results in diminished but still significant SNP-based heritability for anxiety symptoms [23], indicating shared but also specific genetic effects of MDD and anxiety. Genetic correlations have additionally been observed between anxiety and other psychiatric disorders (e.g., schizophrenia, ADHD), sleep, and cardiometabolic traits and risk factors [22, 23]. GWAS of internalizing disorders in youth showed strong genetic correlations (rG > 0.7) with adult anxiety. However, the observed correlations with adult anxiety disorders were partial rather than complete, indicating that from a developmental perspective, childhood/adolescent internalizing symptoms are not genetically identical to adult anxiety or depression [25]. Given these differences, further clarification of specific genetic contributions to youth anxiety is needed.

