## Methods

### Aims

In the current article we outline the design and methods of the GAYA study that aims to better understand the genetic underpinnings of anxiety disorders in Canadian youth. The GAYA study will help close the above-identified gaps in existing research in youth anxiety through a framework of integrated specific aims that will enhance our understanding of the specific genetic contributions to anxiety from childhood through adolescence, and implications for treatment. The specific aims and hypotheses are outlined in Table 1.

**Table 1 Tab1:** Specific aims and hypotheses

	Specific Aim	Hypothesis
**1**	Identify genetic risk factors associated with clinical symptoms and vulnerability markers of youth anxiety.	Each clinical symptom and vulnerability marker will be associated with common genetic variations.
**2**	Identify genetic factors that are unique to anxiety in different age groups.	If the overlap in genetic risk factors is partial between different age groups, then the non-overlapping part will be driven by associations with common genetic variants.
**3**	Identify genetic factors that are shared and unique between anxiety and its common comorbidities.	If pleiotropy is driving co-occurrence of anxiety and common comorbidities, then these traits will have shared genetic risks.
**4**	Identify a prediction model of treatment response in youth with anxiety disorders.	Response to CBT in youth anxiety will be predicted using data from common genetic variation, clinical symptoms, and vulnerability markers.

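### The Aim 3 robustness checks for Mendelian randomization (MR-Egger, MR-RAPS) share with IVW an assumption that would fail if the shared genetic risk hypothesised in the same aim is present

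*Protocol article*

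**What the plan says.** The protocol article, under Specific aim 3, states that "Two-sample Mendelian Randomization (MR) analyses will be conducted using the inverse-variance-weighted (IVW) MR method". The purpose given for this analysis is to "investigate associations between the genetic liability for youth anxiety and adult-onset mental disorders". It then gives the safeguard: "while further ensuring the robustness of our IVW estimates through MREgger and the MR robust adjusted profile score approach". No other MR method is named.

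The hypothesis for this aim (Table 1, under Aims) reads: "If pleiotropy is driving co-occurrence of anxiety and common comorbidities, then these traits will have shared genetic risks". In the same section, just before the MR plan, genomic SEM is intended to "identify loci that confer risk to multiple disorders (i.e., that are shared across disorders").

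The Background reports that large anxiety GWAS show "strong positive genetic correlations with major depressive disorder (MDD) (rG = 0.78") and that GWAS of youth internalizing disorders show "strong genetic correlations (rG > 0.7) with adult anxiety". It also notes that "GWAS studies of anxiety phenotypes in youth have thus far been unsuccessful in identifying any genome-wide significant loci". Specific aim 1 plans to meta-analyse GAYA with other samples.

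**The concern.** MR-Egger allows pleiotropic effects with a non-zero mean. MR-RAPS allows weak instruments, overdispersion and a few outliers. Both, like random-effects IVW, still need each variant's pleiotropic effect to be independent of its strength on the exposure (the InSIDE condition). If a common liability drives both youth anxiety and the adult disorder, variants that act strongly on one through that liability also act strongly on the other, and InSIDE fails. The aim therefore names as safeguards two methods that do not protect against the situation it hypothesises.

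LDSC and genomic SEM in the same aim will describe the sharing, but the article does not carry their results into the MR, for example through the choice of instruments or a rule for interpretation. What is at stake is a significant MR slope that reflects shared genetics being taken as evidence of direction from youth anxiety to later disorder, with the named checks cited in support.

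**Working it through.** The article gives no MR sample size, instrument threshold or power, so there is no stated figure to reproduce. The check is algebra followed by simulation with a true causal effect of zero.

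**Algebra.** Let variant j have effect βx on youth anxiety and βy = θ·βx + α on the outcome, where α is its pleiotropic effect.

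- IVW estimates Σw·βx·βy / Σw·βx², so its bias is Σw·βx·α / Σw·βx².
- If a fraction q of instruments act through a shared factor with α = k·βx, the bias is about k·q.
- Example with θ = 0, q = 0.3, k = 0.8: 0.8 × 0.3 = 0.24. Example with q = 0.8, k = 0.97: 0.97 × 0.8 = 0.776. The simulated IVW slopes with the largest exposure sample were 0.24 and 0.76.
- Pleiotropy of this form passes through the origin. It loads on the MR-Egger slope rather than the intercept, so the intercept test has little to detect except through measurement error in βx.

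**How many instruments.** Assumptions, not in the article: heritability h² = 0.10 over M = 2,000 loci with normal effects. A locus z-score then has variance 1 + N·h²/M, and the expected count is M × 2 × Φ(−z_crit/√variance).

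- N = 13,000 (GAYA alone): variance 1 + 0.65 = 1.65, SD 1.285. At 5e-8, 5.451/1.285 = 4.24, giving about 0.04 instruments. At 5e-6, 4.565/1.285 = 3.55, giving about 0.8.
- N = 50,000 (assumed after meta-analysis): variance 1 + 2.5 = 3.5, SD 1.871. At 5e-8, 5.451/1.871 = 2.91, giving about 7. At 5e-6, 4.565/1.871 = 2.44, giving about 29.

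**Simulation 1.** Exposure n = 50,000 and outcome n = 200,000 (assumed). A fraction of loci equal to the genetic correlation (rG) has identical effects on both traits, and there is no causal path. Share of runs with IVW significant at 0.05:

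| Instruments | rG 0.3 | rG 0.5 | rG 0.7 |
|---|---|---|---|
| about 7 (5e-8) | 30-34% | 57% | 81-82% |
| about 29 (5e-6) | 77% | 98% | 100% |

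Ranges show repeat runs of the set-up. With 7 instruments the rate at rG 0 was already 11%, so part of that row is small-sample inflation. Another run with 29 instruments gave 93.5% at rG 0.3 and 3.5% at rG 0, so the figure at rG 0.3 depends on architecture choices. The MR-Egger intercept was significant in about 4-8% of runs, and the MR-Egger slope in about 6-16%.

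**Simulation 2, including MR-RAPS.** Assumptions: 1,000 loci, h² = 0.10 for each trait, outcome n = 300,000, instruments chosen in an independent sample, 300 replicates. Exposure n was 13,000, 64,641 or 200,000 with thresholds 1e-3, 5e-6 and 5e-8 (about 30, 95 and 234 instruments). Rejection rates are ranges over the three sizes:

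| Shared fraction (rG) | IVW | MR-RAPS | Egger slope | Egger intercept |
|---|---|---|---|---|
| Control: independent pleiotropy | 3-6% | 3-8% | 5-7% | 6-7% |
| 0.1 (0.08) | 31-100% | 6-84% | 9-19% | 4-9% |
| 0.3 (0.24) | 84-100% | 42-100% | 16-63% | 10-11% |
| 0.5 (0.40) | 99-100% | 92-100% | 27-92% | 14-21% |
| 0.8 (0.78) | 100% | 100% | 62-100% | 32-56% |
| 1.0 (0.78) | 100% | 100% | 97-100% | 68-100% |

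In the control row the three methods behave as designed. In the last row every instrument has the same ratio of effects, which looks exactly like a causal slope, so the rows from 0.3 to 0.8 are the more informative ones.

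**The case against.** The strongest case on the other side has five parts.

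- **No causal claim is written.** A reader might infer that the plan will present shared genetics as an effect of youth anxiety. The article does not support that: it speaks of associations of liability, and Table 1 is conditional. Its remarks on early intervention concern the study's results overall and are not tied to the MR. This stands. The point that survives is narrower: association of liability is already addressed by LDSC in the same section, so MR with pleiotropy checks adds something mainly when read directionally.
- **The correlations do not prove a violation.** A high rG can come from a causal path as well as from a shared factor. The 0.78 is for anxiety GWAS in general with MDD, and the figure above 0.7 is for youth internalizing disorders with adult anxiety. This stands, and the point is therefore conditional on the aim's own hypothesis.
- **The three methods may not agree.** A reader might expect MR-Egger to confirm a spurious IVW result. In Simulation 1 its slope was significant in only about 6-16% of runs, so it usually would not. That partly reflects low power, and a non-significant MR-Egger slope does not tell a reader that sharing is the cause. MR-RAPS also reduces the bias when few instruments are shared.
- **Instruments may be few.** The absence of genome-wide loci describes earlier youth studies, and meta-analysis is planned, so it cannot be concluded that MR will be impossible.
- **This is a condensed article.** Further sensitivity methods may sit in a fuller plan. That is fair for omissions, but the article makes a positive statement about what secures robustness, and that statement is what is questioned here.

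**Conclusion.** The point holds in a conditional form. If the shared genetic risk of Aim 3 is present, IVW, MR-Egger and MR-RAPS all lose the assumption they rely on, and the two checks cannot be said to ensure the robustness of IVW. With no causal effect, IVW was significant in about 34-81% of runs with 7 instruments and 77-100% with 29 at rG 0.3-0.7. The MR-Egger intercept rarely warned in that setting, but warned in 32-56% of runs in the second simulation with 80% of loci shared. The direction follows from the algebra. The sizes rest on assumed heritability, locus number, sample sizes and thresholds, none of which the article gives.

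It does not follow that a false directional finding is to be expected, or that the three methods are unsuitable and should be removed. This is an inexpensive improvement to one component of Aim 3, not a flaw in the study as a whole.

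**What to change.** In the MR text of Specific aim 3:

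1. Keep IVW, MR-Egger and MR-RAPS.
2. Add a method that models correlated pleiotropy (CAUSE or latent causal variable analysis), and run MR in the reverse direction.
3. Replace the assurance of robustness with a statement that MR-Egger and MR-RAPS do not cover pleiotropy through a shared factor.
4. State the reporting rule: a result is described as shared genetic liability, not as a directional effect, unless the causal model fits better than the shared-factor model.

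The cost is a change of wording and a little more analysis of summary statistics, with no new data. The downsides are fewer directional claims and possibly low power of the added methods if few youth loci emerge.
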